### Sample size and power calculation

Assuming that the source analyses are focused on transmission to the index children, and after accounting for the anticipated accrual goal and drop-out rate, a total of 1500 samples from 100 children (13 non-diarrheal and 2 diarrheal stools per index child on average from recent HDSS data) will be included in the analysis. We assumed a design effect of 1.7 to account for correlation between samples from same child, based on the intraclass correlation coefficient of (ICC) 0.05 for *Shigella* and *Campylobacter* detections within samples from the same child in the MAL-ED study^[2]^. We assume the design effect will be similar across *Shigella* and individual *Campylobacter* species. Assuming that 10% of each type of environmental sample tests positive for the target pathogen and the overall prevalence of pathogen infection is 20%, we would have 80% power to detect a risk ratio of 1.76 for each pathogen species and environmental pathway in a two-sided test with alpha=0.05. The minimum detectable risk ratio at 80% power varies by the proportion of environmental samples that test positive for the pathogen and by alternative assumptions for the design effect (Figure 1). Over a range of plausible design effects and pathogen prevalence in varied environmental sample types, we will have power to detect risk ratios that will identify the most important transmission pathways for *Shigella* and the most prevalent individual *Campylobacter* species.

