### Data analysis

The goals of the analysis are to identify possible sources and transmission pathways for *Shigella* and *Campylobacter* using two complementary approaches of statistical and mathematical modeling, whereby the former helps inform the latter. Specifically, we will generate measures of disease incidence, pathway-specific relative risks, environmental contact rates, and duration of pathogen shedding, all of which will inform and parameterize the transmission models. We will then develop complementary transmission models to characterize the relative importance of person-to-person and environmental transmission.

To identify potential sources for infections in index children, we will compare the prevalence of the target pathogen in environmental and familial samples between infected and uninfected index children. We will evaluate possible sources for *Shigella* as well as for *Campylobacter* species identified in at least 5% of stool samples from index children. Source types will be categorized into six pathways with their respective sample types: people (samples: caregiver and sibling stools), animals (animal feces), flies, food, water, and soil. Pathogen burden in each pathway will be characterized as the total qPCR Cq-derived quantity of species-specific pathogen detected in samples from that pathway. The duration of convalescent shedding will be estimated based on the median time from the onset of symptoms to the final positive convalescent stool performed on all qPCR-positive convalescent stool samples.

We will estimate the associations between pathogen quantity in an environmental pathway and infection in the index child using log-binomial regression with generalized estimating equations to account for correlation between samples from the same child over time. We will adjust for age and month of the year given the expected seasonality of exposure. Using the estimated relative risks for each transmission pathway, we will estimate attributable fractions (AF), where AF = 1 – 1/RR and RR is the relative risk for each pathway. We have previously used the attributable fraction methodology to attribute diarrhea etiologies^[18,27]^, a metric that accounts for both the prevalence of detection in a given pathway as well as the strength of association with infection and will provide a rank ordering of the relative importance of each pathway. The estimated relative risks will be used in the transmission models as described below.

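### The attributable fraction 1 – 1/RR contains no prevalence term although the protocol says it accounts for prevalence, so the pathway ranking is a ranking by RR alone and can misorder pathways that differ in detection prevalence

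*Protocol article*

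**What the plan says.** The Data analysis section groups potential sources into people, animals, flies, food, water and soil: "Source types will be categorized into six pathways with their respective sample types". It will estimate "associations between pathogen quantity in an environmental pathway and infection in the index child using log-binomial regression", using generalized estimating equations and adjusting for age and calendar month.

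From these relative risks it derives an attributable fraction, "where AF = 1 – 1/RR and RR is the relative risk for each pathway". The next sentence calls this "a metric that accounts for both the prevalence of detection in a given pathway as well as the strength of association with infection" and says that it "will provide a rank ordering of the relative importance of each pathway". On the later modelling, the section states: "The estimated relative risks will be used in the transmission models as described below".

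The only numeric scenario in the text is in Sample size and power calculation. It assumes 10% of each environmental sample type positive and 20% infection prevalence overall, and concludes that "we would have 80% power to detect a risk ratio of 1.76 for each pathogen species and environmental pathway". The same section says that prevalence will vary between sample types, but its text gives no figures for this.

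**The concern.** Two adjacent sentences disagree. The formula takes one input per pathway, the RR. The description says that the result also reflects how often the pathogen is found in that pathway. Both cannot be true of 1 – 1/RR.

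The description is what justifies the ranking. The primary objective is to identify sources and routes, with targeted interventions as the goal. For that purpose, a pathway that is rarely contaminated but strongly associated with infection may account for fewer infections than one that is often contaminated and moderately associated. A measure that combines prevalence and strength would show this. The stated formula cannot, so a reader who trusts the description could take an order of strength for an order of burden.

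**Working it through.** **Inputs.** From Sample size and power calculation: 1500 samples, design effect 1.7, 10% of environmental samples positive, 20% infection overall, two-sided alpha 0.05, RR 1.76. From Data analysis: AF = 1 – 1/RR. All other prevalences and RRs below are assumptions, because the text gives none.

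**The plan's own figure.** Effective N = 1500/1.7 = 882.4, that is 88.2 exposed and 794.1 unexposed. Infection risk in the unexposed is 0.20/(0.9 + 0.1 × 1.76) = 0.186, and in the exposed 1.76 × 0.186 = 0.327. A continuity-corrected two-proportion test then has 81.8% power at RR 1.76, and its minimum detectable RR at 80% power is about 1.74. Without the correction, the minimum is 1.70 (pooled variance), 1.79 (unpooled) or 1.64 (log-RR). The stated 1.76 is therefore reproduced closely enough, and it refers to a positive/negative exposure.

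**Stated AF against population AF.** Let p be the share of all samples with the pathway positive, and p_c the share among infected samples.

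- Stated: AF = 1 – 1/RR
- Population: PAF = p_c × (1 – 1/RR), with p_c = p × RR / (1 + p(RR – 1)). Without confounding this equals p(RR – 1) / (1 + p(RR – 1)).

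At RR 1.76 and p = 0.10: AF = 1 – 1/1.76 = 0.432; p_c = 0.176/1.076 = 0.164; PAF = 0.164 × 0.432 = 0.071.

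Holding RR at 1.76 and varying p:

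| Samples positive | Stated AF | PAF |
|---|---|---|
| 2% | 43.2% | 1.5% |
| 5% | 43.2% | 3.7% |
| 10% | 43.2% | 7.1% |
| 20% | 43.2% | 13.2% |
| 50% | 43.2% | 27.5% |
| 80% | 43.2% | 37.8% |

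The stated AF does not move with prevalence.

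**Effect on the ranking.** 1 – 1/RR rises strictly with RR, so ranking by it is ranking by RR. PAF rises strictly with p(RR – 1), so the PAF order is the order of p(RR – 1). For pathway A with RR 3.0 and pathway B with RR 1.5, B ranks above A on PAF when 0.5 p_B > 2 p_A, that is when p_B > 4 p_A.

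- A at 5%, B at 50% (assumed): AF 66.7% and 33.3%; PAF 0.10/1.10 = 9.1% and 0.25/1.25 = 20.0%. The order reverses. With A at 5%, B must exceed 20% for this.
- A at 2%, B at 50% (assumed): AF is unchanged; PAF 0.04/1.04 = 3.8% and 20.0%. The order reverses.
- Equal prevalence, or the higher-RR pathway also the more prevalent: both measures give the same order.

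**The case against.** The strongest defence is that this is a gap in wording and not in method. The RR is modelled on pathogen quantity, and the section cites the investigators' earlier use of attributable fractions for diarrhea etiologies. If 1 – 1/RR is evaluated at each infected sample's own quantity, with RR = 1 where nothing is detected, and then averaged over all infected samples, prevalence does enter. A check with assumed levels (90% of samples at RR 1, 6% at RR 1.5, 4% at RR 2.15) gives 0.0706 by this averaging and 1 – 1/1.076 = 0.0706 by the population formula. The authors may intend this. However, the text names a single RR per pathway and states no averaging step, nor does it say how prevalence entered the earlier work. An article may leave detail to a fuller plan, but here it prints a formula and gives it a property that it lacks.

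Other parts of the defence stand, and they limit the point. A reader might infer four stronger things that the documents do not support:

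- *That the ranking will be wrong.* It can be. The only numeric scenario has 10% for every sample type, and at equal prevalence the two orders agree.
- *That the stated AF is inflated several-fold.* The 43% and the 7% are different estimands. The first is a correct attributable fraction among the exposed. The fault lies in its description and its use for ranking.
- *That the AF depends on an arbitrary unit of quantity.* This would need a continuous per-unit RR. The sample size section works with a positive/negative exposure, and the transmission-modelling paragraph speaks of associations between detections, so the form of the RR is not settled.
- *That the error carries into the transmission models.* They take the RRs and not the AFs.

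**Conclusion.** The point holds as a contradiction between a stated formula and its stated property. As written, the AF ranking adds nothing to a ranking by RR, and it can misorder the six pathways when detection prevalence differs between them, which the protocol itself expects. In the plan's own scenario, 43% describes infections among exposed samples only; the corresponding share of all infections is 7%. Whether any order actually reverses depends on prevalences and RRs that the text does not give. For RRs of 3.0 and 1.5, it takes more than a four-fold difference in prevalence in favour of the weaker association. RR estimation, data collection and the transmission models are not affected.

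**What to change.** Replace the formula in Data analysis with the population attributable fraction, PAF = p_c × (1 – 1/RR), where p_c is the share of infected index-child samples with the pathway positive, among visits at which that pathway was sampled. This form suits the planned RRs adjusted for age and month, because it uses prevalence among the infected. If the RR is modelled on quantity, use instead the mean over infected samples of 1 – 1/RR(q_i), with RR(q_i) taken at the observed quantity against non-detection; this also fixes the reference contrast. If that averaging is already intended, stating it is enough. Obtain intervals by bootstrapping children, and rank on PAF.

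Deleting the claim about prevalence would also make the text consistent, but the ranking would then be by strength of association only and should be labelled so.

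The cost is a little more analysis work and smaller reported fractions. No new samples are needed. A rule is needed for visits at which a pathway was not sampled: under Soil, homes with cement floors give no sample, and under Milk and maize porridge samples, food is taken only if it is available that day.

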The goal of the infection transmission modeling is to understand where the transmission of different enteric pathogens falls on the continuum from primarily person-to-person to primarily environment-to-person transmission, using *Shigella* and *Campylobacter* as model organisms. Our infectious disease transmission modeling approach will consist of two complementary frameworks. First, we will develop an individually based household dynamic transmission model to capture the PCR-confirmed incidence of clinical and subclinical *Shigella* and *Campylobacter* infections observed in this study. Prevalence and duration of shedding in convalescent stools will help to parameterize two model parameters: shedding rate and a factor converting shedding from humans into increases in environmental contamination. Second, we will use a compartmental model framework to develop an endemic transmission model of the cohort. We will incorporate the prevalence of collected household characteristics, environmental contacts and measured environmental exposures (water, food, flies, etc.). Finally, relative risks estimated from the associations between detections in environmental and familial samples and infections in the index child will provide informative priors for parameters that characterize the importance of person-to-person and environmental transmission.

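### Relative risks from this study's index children become informative priors for transmission models of the same cohort, so index-child data are used twice and posterior uncertainty is understated

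*Protocol article*

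**What the plan says.** The Data analysis section of the Protocol article describes two linked stages.

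- **Regression stage.** Pathway-specific relative risks for index-child infection are estimated by log-binomial GEE on the index children's repeated samples, adjusted for age and calendar month. The section adds: "The estimated relative risks will be used in the transmission models as described below".
- **Transmission stage.** The first model is an "individually based household dynamic transmission model to capture the PCR-confirmed incidence of clinical and subclinical" *Shigella* and *Campylobacter* "infections observed in this study". The second uses a "compartmental model framework to develop an endemic transmission model of the cohort". The closing sentence says that relative risks relating what is detected in environmental and family samples to "infections in the index child will provide informative priors for parameters that characterize the importance of person-to-person and environmental transmission".

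The Abstract adds that the timing of infection cases will be analysed with transmission models. The stated goal of the modelling is to place each pathogen on the continuum between the two routes. The article mentions no external source for these priors, no cut or joint model, and no down-weighting.

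**The concern.** A prior should carry information that is not already in the data being fitted. Here the index-child infections shape the prior through the relative risks and are also among the infections the model must reproduce. The overlap falls on the parameters that answer the modelling question, so the resulting intervals would claim more information than the study holds.

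Bias is carried over as well. The transmission stage includes a factor turning human shedding into environmental contamination, so the plan accepts that infected people contaminate their surroundings. The stated regression adjusts only for age and month. Its relative risks can therefore mix exposure leading to infection with infection leading to contamination. A dynamic model is the tool for separating those directions, and an informative prior built on the unseparated association pulls it back towards that association.

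**Working it through.** **1. Scale of the relative risks.** The modelling text gives no figure, so the precision is taken from Sample size and power calculation: 1500 samples from 100 children (15 each), ICC 0.05, design effect 1.7, 10% of environmental samples positive, 20% infection prevalence, and 80% power at a risk ratio of 1.76, two-sided 0.05.

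- Design effect: 1 + (15 − 1) × 0.05 = 1.70, as stated.
- Effective sample: 1500 / 1.7 = 882, or 88 exposed and 794 unexposed.
- With 20% as the overall prevalence and a risk ratio of 1.76: p0 = 0.20 / (0.9 + 0.1 × 1.76) = 0.186 and p1 = 1.76 × p0 = 0.327.
- Power at 1.76: 81.8% for a two-proportion test with continuity correction, 84.8% pooled without it, 77.8% unpooled. The stated 80% is reproduced to within two points by the first.
- SE(log RR) = sqrt[(1 − p1)/(n1·p1) + (1 − p0)/(n0·p0)] = 0.170.

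**2. Full overlap.** Let the prior come from the fitted data themselves, with precision w times that of the data. The posterior stays centred on the same estimate, but its SD is multiplied by 1/sqrt(1 + w). True coverage of a nominal 95% interval is 2Φ(1.96/sqrt(1 + w)) − 1.

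**3. Partial overlap.** Let the fitted data hold k times the index-child information, and let the prior hold all of the index-child information once more. The claimed variance is proportional to 1/(k + 1). The estimate counts the index-child part twice, so its true variance is proportional to (k + 3)/(k + 1)². Claimed SE over true SE is sqrt[(k + 1)/(k + 3)], and coverage is 2Φ(1.96 × that ratio) − 1.

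| Case (w and k are assumed) | Claimed SE / true SE | Coverage |
|---|---|---|
| Full overlap, w = 1 | 0.71 | 83.4% |
| Full overlap, w = 0.5 | 0.82 | 89.0% |
| Full overlap, w = 0.25 | 0.89 | 92.0% |
| Full overlap, w = 0.1 | 0.95 | 93.8% |
| Partial overlap, k = 2 | 0.77 | 87.1% |
| Partial overlap, k = 4 | 0.85 | 90.2% |
| Partial overlap, k = 6 | 0.88 | 91.6% |

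**4. Illustration on the relative-risk scale.** At a risk ratio of 1.76 with SE 0.170, the 95% interval is 1.26 to 2.45 when the data are used once. Using them twice at equal weight (SE divided by sqrt 2) gives 1.39 to 2.23.

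Coverage is below 95% in every case. The direction follows from the text. The size depends on w and k, which the article does not give.

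**The case against.** The strongest reply is that the article describes a model developed to capture incidence and never sets out a likelihood, a fitting algorithm, a prior width, a mapping from relative risk to transmission parameter, or a posterior interval. Such details commonly sit in a fuller document that is not shown. The sentence on priors follows the compartmental model, and the article does not say which of the two models receives them or what data the compartmental model is fitted to. The relative risks use index children only, whereas stools are collected from all household members, so the overlap is partial. The plan is also openly sequential: the regression is meant to inform the models.

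Much of this stands, and it limits the size. It does not remove the point. Informative priors have a role only if the models are updated with data; the Abstract names the infection cases as what the models analyse; both models concern this cohort. The source of the priors is a stated choice, not an omitted detail. Feeding separately measured inputs such as contact rates into a model is sound. Feeding in an estimate from the same outcomes as an informative prior is not.

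A reader might also infer that the plan offers agreement between its two approaches as independent confirmation. It does not: it calls them complementary and says that one informs the other.

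**Conclusion.** The point holds in direction. Followed as written, the plan uses index-child infections in both the prior and the fitted data for the parameters that place each pathogen on the continuum, and it understates their uncertainty.

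A reader might infer that the intervals will be 29% too narrow with 83% coverage. The documents do not support that as an estimate. It is the worst case, with complete overlap and a prior weighted equally with the data. If other household members' infections make total information 2 to 6 times that of the index children, coverage is about 87% to 92%; a lightly weighted prior loses less. All these figures assume normality and a single parameter.

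A reader might also infer that the study's main source findings are compromised. They are not: the relative-risk and attributable-fraction analysis, to which the power calculation applies, does not use these priors, and the article ties no decision rule to a posterior interval. This is a point that should be fixed before the models are fitted, not one that invalidates the study.

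**What to change.** In the closing sentence of Data analysis, replace the study-derived informative priors with one of two options:

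- weakly informative priors for the person-to-person and environmental parameters, or priors from external data where such data exist; or
- one joint model that estimates the associations and the transmission parameters together, so that each infection is used once.

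In either case, keep this study's relative risks as a posterior predictive comparison: simulate from the fitted model, derive the relative risks it implies, and set them beside the regression estimates. Amend the earlier sentence that passes the relative risks to the models so that it describes this use.

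External priors may be hard to find. The earlier cohort cited in the sample size section is used there only for its ICC, and the article does not show that it measured environmental pathways.

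The weakly informative option changes only the wording of the modelling plan; a joint model takes more modelling work. Neither changes a visit, sample or assay. The statistical price is wider posterior intervals and possibly weaker identification of some parameters, which should be shown by a prior-sensitivity analysis reported with the results.

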## ETHICS AND DISSEMINATION

The study was granted an ethical approval and registered by the National Institute for Medical Research (NIMR) in Tanzania (NIMR/HQ/R.8a/Vol.IX/4023) and the University of Virginia Institutional Review Board (HSR210431) in the US. Permission to conduct the study was granted by the local leaders in the study catchment area and the HLH administrative authorities. Prior to any study procedure, all members of eligible households will consent to participate in the study, provide sociodemographic, clinical information, specimens for laboratory testing and their microbiological information to be used in the study. Each household approached for participation will be informed about the study, and if found eligible for enrollment will go through a voluntary consent process. This will include informed consent of adults and of parents/guardians for children under 18 years of age. For children 7–17 years of age, verbal assent will also be obtained. For both the consent and assent, participants will have the opportunity to ask questions and review the study information and consent/assent forms. They do not need to consent/assent right away but will have time to think about their response and ask any questions about the protocol/study. They will be encouraged to seek advice from friends and family before signing consent. All subjects will be asked open-ended questions to confirm that they understand the study. For the potential participants who are illiterate, they will be allowed to identify an impartial witness who will participate in the consenting process. If they understand and consent to participation in the study, they will mark with a thumbprint and the impartial witness will sign the consent. A copy of the signed informed consent form will be given to all participants.

The scientific reports resulting from this study will be made publicly available, through publication in open-access journals and conference presentations. Data will be made available in a public repository. An integrative knowledge translation strategy will be used for involving policy makers and key stakeholders at the Ministry of Health in Tanzania and beyond.

